Some rats died after single intravenous doses  $\geq 90$  mg/kg during experiments designed to push to the highest maximum tolerated doses of the drug. The cause of death was undetermined. The  $\geq 90$  mg/kg dose is approximately 60-fold higher than the planned starting dose in humans of 0.25 mg/kg, based on body surface area calculations.

In safety pharmacology studies, no adverse findings were observed for any of the major organ systems evaluated.

Illuminare-1 was not mutagenic in a bacterial reverse mutation assay (Ames test) but did cause chromosome aberrations in an *in vitro* human peripheral lymphocyte assay under certain test conditions. When Illuminare-1 was given to rats by intravenous bolus injection as a daily dose for 3 days (dose levels up to 65 mg/kg/day), it was not genotoxic in either the comet assay with the liver or the bone marrow micronucleus assay. When considering the results of all the genotoxicity studies together, the weight of evidence demonstrates that Illuminare-1 is not genotoxic.

In an *in vitro* study in BALB/c 3T3 mouse fibroblasts, Illuminare-1 showed phototoxic potential, with an IC50 of 0.650 µg/mL. Additionally, as grade 1 erythema was seen at 24 and 48 hours post-injection on unprotected skin of pigmented rats, precautions will be taken for the first 48 hours after drug administration. Medications with known phototoxic potential will be avoided and patients will avoid excessive ultraviolet light exposure (patients remain in the hospital until the day after surgery per standard of care and will wear opaque clothing once discharged until 48 hours post-injection).

Exposure limits for the first-in-human study were established on the basis of findings in the pivotal single-dose intravenous studies in rats and dogs. The NOAEL in the dog study was 18 mg/kg (the highest dose tested), and the NOAEL in the rat study was 20 mg/kg. Given the findings in rats, this was considered the most sensitive species, and a conservative approach was taken for the selection of the starting human dose (0.25 mg/kg), which is approximately 13-fold less than the NOAEL in rats. In addition, clinical monitoring of renal function will be performed in this study.

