## **6.2 Participant Exclusion Criteria**

Exclusion from the study will occur for patients with the following:

- Prior pelvic surgery or pelvic radiation therapy
- Known central nervous or peripheral nervous system disease or insult (including neurodegenerative diseases), current use of neurotoxic medications, or use of cytotoxic chemotherapy with known neurotoxicity within 1 month
- Exposure to investigational agents in the immediate 30 days before or 15 days after study drug administration
- Patients with significant renal dysfunction (<60 mL/min as assessed by the Cockcroft Gault calculation for creatinine clearance)
- Clinically significant hepatic/liver impairment (liver function tests more than 2x institutional normal upper limit)
- Exposure to phototoxic drugs such as St. John's wort, griseofulvin, thiazide diuretics, sulfonyleureas, phenothiazines, sulphonamides, quinolones, and tetracyclines, should be avoided. If safe to discontinue use for a limited time, patients may participate on this trial but will discontinue the use of the interfering drug for 5 half-lives before Illuminare-1 injection to permit full washout, as well as for 48 hours after administration of Illuminare-1.

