11. Patients exposed to a photosensitizing agent may experience a phototoxic skin reaction, such as a sunburn, when exposed to excessive ultraviolet light or phototoxic drugs. As a precaution and because the half-life of the agent is approximately 4 hours, we will avoid administration of phototoxic drugs such as St. John's wort, griseofulvin, thiazide diuretics, sulfonylureas, phenothiazines, sulphonamides, quinolones, and tetracyclines for 24 hours before and after administration of Illuminare-1. These medications are uncommonly administered during the standard preoperative and postoperative pathway for patients undergoing minimally invasive radical prostatectomy.
12. Patients will be evaluated prior to discharge on postoperative day 1 and repeat neurologic examinations performed at baseline will be performed. Patient will also receive a CTN telephone call within 2 days of surgery for toxicity evaluation.
13. Patients will be evaluated at the postoperative visit on POD 10 (+/- 5). Repeat neurologic examinations performed at baseline will be performed. One tube of blood will be drawn for future research purposes under MSK IRB#06-107 or MSK IRB#12-245.

14. Patients will be evaluated at a postoperative visit on POD 30 (+/- 5) with a telephone follow-up. Patients are not routinely seen between the day 10 visit and the first PSA lab assessment so a telephone visit to assess for toxicity will be performed and if necessary, an in-person visit will be coordinated if there is clinical concern.
15. Patients will be evaluated at the postoperative visit on POD 45(+/- 10) corresponding to the first PSA blood level assessment. Repeat neurologic examinations performed at baseline will be performed. One tube of blood will be drawn for future research purposes under MSK IRB#06-107 or MSK IRB #12-245.

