## Investigational Agent Evaluations

Subjects will remain in-patient after administration of Illuminare-1 for 24 h before discharge. During this period, the patients will be monitored for adverse events according to CTCAE 5.0.

At 10 ( $\pm$  5) days, patients will be assessed during the routinely scheduled postoperative visit which may coincide with catheter removal. Patients will also be questioned about adverse events at 30 ( $\pm$  5) days via telephone, and at the first postoperative PSA lab assessment, which typically occurs around 7 weeks after surgery ( $45 \pm 10$  days).

The pharmacokinetics of Illuminare-1 will be evaluated from blood drawn at baseline, 15, 30, 120, 240, 480 minutes (all  $\pm$  10 min), 12 hours ( $\pm$  1h), 18 hours ( $\pm$  2h), and 24 hours ( $\pm$  2h) after injection in all patients. In addition, a minimum of 3 patients in each dose cohort will also have blood drawn at 48 hours ( $\pm$  24h) and 72 hours ( $\pm$  24h) after administration for pharmacokinetics evaluation. A minimum of 3mL whole blood will be collected into 5 mL EDTA purple top tubes. Handling instructions (e.g., sample processing, centrifugation, storage conditions) will be provided to the processing laboratory via SOP prior to sample collection. One tube of blood ( $<10$ cc) will be drawn and stored for potential future research investigations at in-person follow-up visits 10 days ( $\pm$  5 days) post-surgery and the first PSA blood draw ( $45 \pm 10$  days). The samples for future research will be taken under MSK IRB#06-107 or MSK IRB#12-245. All pharmacokinetics analyses will be performed using Phoenix WinNonLin (version 8.1) and a noncompartmental approach consistent with the intravenous route of administration. Pharmacokinetics model selection will be based on a visual inspection of goodness-of-fit plots (observations vs. predictions, residuals and weighted residuals vs. predictions). The assay values (concentrations vs. times) measured using a validated LC-MS method will be used to calculate half-life, volume of distribution, clearance, individual-specific elimination rate constant ( $K_e$ ), time to maximum concentration ( $T_{max}$ ), maximum concentration ( $C_{max}$ ), and area under the concentration–time curve (AUC) values. Pharmacokinetic analyses will be conducted at MSK by core facilities and the statistician will not perform these.

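### Section 10, item 11 avoids phototoxic drugs for only 24 hours after dosing, half the 48 hours set in Section 6.2 and Section 3

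*Protocol*

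**What the plan says.** Three places in the Protocol bear on how long phototoxic drugs are to be avoided.

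- **Section 10.0, item 11 (treatment plan).** The listed drugs are to be avoided "for 24 hours before and after administration of Illuminare-1". The reason offered is the agent's own elimination: "because the half-life of the agent is approximately 4 hours, we will avoid administration of phototoxic drugs".
- **Section 6.2 (exclusion criteria).** For the same eight drugs and drug classes, a patient who can safely stop may take part, but must stay off the drug "for 5 half-lives before Illuminare-1 injection to permit full washout, as well as for 48 hours after administration of Illuminare-1".
- **Section 3.0, Nonclinical Studies.** After reporting in vitro phototoxic potential, the section notes that "grade 1 erythema was seen at 24 and 48 hours post-injection on unprotected skin of pigmented rats" and concludes that "precautions will be taken for the first 48 hours after drug administration". The next sentence begins: "Medications with known phototoxic potential will be avoided and patients will avoid excessive ultraviolet light exposure".

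Nothing in the Protocol says which window prevails.

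**The concern.** Item 11 sits in the treatment plan, where perioperative staff look for what they may give and when. Its window is shorter than the one in Section 6.2 after dosing and can be shorter before dosing. Someone who follows item 11 to the letter could give or restart a listed drug between 24 and 48 hours, while the patient is still inside the Protocol's own precaution period, and believe that this complies.

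The timing makes the gap practical. Section 11.0 states: "Subjects will remain in-patient after administration of Illuminare-1 for 24 h before discharge". Item 11's restriction thus ends just as the patient goes home, when regular medicines may be resumed or new ones prescribed. The schedule in Section 11.0 places concomitant-medication checks before surgery and within 24 hours after it, and none at 48 hours, so an early restart might not be noticed.

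At stake is an avoidable skin reaction in a first-in-human trial, and a harder attribution question if one occurs. Section 15.0 counts treatment-related non-haematological toxicity of grade 2 or higher as dose-limiting.

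**Working it through.** The Protocol gives no derived figure to reproduce here. The check sets the windows side by side and takes differences.

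**Inputs**

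| Source | Before dosing | After dosing | Stated basis |
|---|---|---|---|
| Section 10.0, item 11 | 24 h | 24 h | Agent half-life about 4 h |
| Section 6.2 | 5 half-lives of the interfering drug | 48 h | Full washout (before dosing) |
| Section 3.0 | not set | 48 h (precautions, including drug avoidance) | Rat erythema at 24 and 48 h |

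**After dosing**

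Gap = 48 h − 24 h = 24 h. Item 11 covers 24 / 48 = half of the required period and leaves hours 24 to 48 open.

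**Before dosing**

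Item 11 satisfies Section 6.2 when 5 × t½ ≤ 24 h, that is, t½ ≤ 24 / 5 = 4.8 h, where t½ is the half-life of the interfering drug. The Protocol gives no half-lives for the listed drugs. The values below are assumptions that show the range and are not tied to any particular drug.

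| Assumed t½ | Section 6.2 requires (5 × t½) | Shortfall of item 11 |
|---|---|---|
| 2 h | 10 h | 0 h |
| 10 h | 50 h | 50 − 24 = 26 h |
| 24 h | 120 h | 120 − 24 = 96 h |

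**The stated reason**

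The agent's half-life can inform a post-dose window. At 4 h, 24 h is 24 / 4 = 6 half-lives, and under simple first-order decay 0.5^6 ≈ 1.6% remains. At 6 h, the upper end of the terminal half-lives reported for rats and dogs in Section 3.0, it is 24 / 6 = 4 half-lives, and 0.5^4 ≈ 6% remains. Section 3.0, however, bases its period on an observed skin effect still present at 48 h in rats, one of the two species with these half-lives of 4 to 6 h. Low plasma concentration at 24 h therefore does not answer the finding that led to the 48-hour rule. Before dosing no agent is in the body, so its half-life cannot fix that window at all. The relevant quantity is the half-life of the other drug, as Section 6.2 recognises.

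**The case against.** The strongest reply is that Section 6.2 already governs. A restart can only concern a patient who was taking a listed drug, and Section 6.2 binds that patient for 48 hours whatever item 11 says. Before dosing, the two rules can both be followed: the patient washes out under Section 6.2, and staff give nothing listed in the last 24 hours. Section 3.0 is also less explicit than Section 6.2. It attaches 48 hours to precautions in general, and the sentence on medications carries no duration of its own. The harm looks small as well: the rat finding was grade 1, patients avoid ultraviolet light and "will wear opaque clothing once discharged until 48 hours post-injection" in any case, and item 11 itself describes the listed drugs as uncommon in this pathway.

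Much of this stands and limits the point. The pre-dose mismatch matters mainly for a listed drug newly given after eligibility is confirmed, and its size rests on assumed half-lives. Applying Section 3.0's 48 hours to drugs is a reading, though a natural one, because drug avoidance is the first precaution named after that period is set.

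The post-dose conflict remains. For a drug newly given around surgery, item 11 is the only operating instruction with an explicit drug window, and it is 24 hours short of the Protocol's precaution period. For a patient who stopped a drug, Section 6.2 does bind, but staff working from the treatment plan read a shorter window for the same drugs.

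**Conclusion.** The concern holds. Item 11 contradicts the 48-hour rule in Section 6.2, and Section 3.0 as naturally read, by 24 hours after dosing. That figure comes directly from the text and needs no assumption. Before dosing, item 11 falls short of the Section 6.2 washout for any interfering drug with a half-life above 4.8 hours; how far short depends on half-lives that the Protocol does not give.

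Item 11 is the one to correct. The 48 hours rest on observed skin findings, and the pre-dose washout rests on the pharmacology of the interfering drug. The agent's half-life supports neither a post-dose window that stops at 24 hours nor any pre-dose window.

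The expected harm is modest. No effect on dose escalation, on an endpoint or on any statistical figure has been shown. The correction should be made because this is a safety instruction in a first-in-human trial that staff can follow exactly and still breach the eligibility rule.

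**What to change.** In Section 10.0, item 11, replace the 24-hour window with: *5 half-lives of the interfering drug before, and 48 hours after, administration of Illuminare-1*. Remove the agent's half-life of about 4 hours as the reason for the window. Sections 3.0 and 6.2 need no change.

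Optionally, add a question about the listed drugs to the telephone call already planned within 2 days of surgery (Section 10.0, item 12).

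The cost is one sentence of item 11. There is no new visit, procedure or sample, and the question at the call is optional.

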### Timeline of Interventions and Assessments

[figure not shown]

### 11.0 EVALUATION DURING TREATMENT/INTERVENTION

|                               | Preop/Eligibility | Perioperative | Postsurgery (<24 h) | Postsurgery (48 h and 72 h post injection) | Postsurgery (day 10 ± 5) | Phone Follow-Up (30± 5 days) | Follow-Up Visit 45 ± 10 days) |
|-------------------------------|-------------------|---------------|---------------------|--------------------------------------------|--------------------------|------------------------------|-------------------------------|
| Informed consent              | X                 |               |                     |                                            |                          |                              |                               |
| Concomitant medication check  | X                 |               | X                   |                                            |                          |                              |                               |
| History and physical exam*    | X                 |               | X                   |                                            | X                        |                              | X                             |
| Multiparametric prostate MRI* | X                 |               |                     |                                            |                          |                              |                               |
| Vital signs*                  | X                 | X             | X                   |                                            | X                        |                              | X                             |
| Karnofsky performance status* | X                 |               |                     |                                            | X                        |                              | X                             |
| Standard presurgical testing* | X                 |               |                     |                                            |                          |                              |                               |

|                                                             |   |   |   |   |   |   |   |
|-------------------------------------------------------------|---|---|---|---|---|---|---|
| CBC (standard) and comprehensive metabolic panel*           | X |   | X |   | X |   | X |
| Urinalysis                                                  | X |   |   |   |   |   |   |
| Urine culture (if indicated)                                | X |   |   |   |   |   |   |
| ECG                                                         | X |   | X |   |   |   |   |
| Research ECG via 24-hour Holter monitor †                   |   | X | X |   |   |   |   |
| Adverse events** CTCAE 5.0                                  |   |   | X |   | X | X | X |
| Neurologic assessment                                       | X |   | X |   | X |   | X |
| Subjective fluorescence assessment of obturator nerve       |   | X |   |   |   |   |   |
| Subjective fluorescence assessment of neurovascular bundles |   | X |   |   |   |   |   |
| Blood sampling for pharmacokinetics ***                     |   | X | X | X |   |   |   |
| PSA lab assessment*                                         |   |   |   |   |   |   | X |
| Blood for future research purposes (under 06-107 or 12-245) |   |   |   |   | X |   | X |
| Ex vivo tissue H&E                                          |   |   | X |   |   |   |   |
| Video evaluation (duration of surgery, NMR)                 |   | X |   |   |   |   |   |

\*Standard of care evaluations.

\*\*Serious adverse events will be reported from the time of informed consent to the end of study evaluation (45 +/- 10 days). Adverse events considered to be related to the drug that are grade ≥2 will be reported from the time of Illuminare-1 administration to the end of study evaluation. Adverse events from the time of informed consent to Illuminare-1 administration will be recorded in the medical history. Postsurgery (<24 hr) AE evaluation will occur via a CTN phone call within 2 days of surgery.

\*\*\*Blood will be drawn at baseline, 15, 30, 120, 240, 480 minutes (all +/- 10min), 12 hours (+/- 1h), 18 hours (+/- 2h), and 24 hours (+/- 2h) after injection for pharmacokinetics evaluation in all patients. In addition, a minimum of 3 patients in each dose cohort will also have blood drawn at 48 hours (+/- 24h) and 72 hours (+/- 24h) after administration for pharmacokinetics evaluation.

† ECG extraction timepoints: 3 baseline timepoints preoperatively; 0.25, 0.5, 2, 4, 8, 12 and 24 hours post-dose to align with PK timepoints. Patients to be comfortably resting in a supine position for ~10 minutes, the first 5 minutes to allow the heart rate and autonomic tone to stabilize, and the second 5 minutes for the ECG 'extraction window'. Exact timepoints will be recorded.

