## Part 2 – Expansion Cohort

### Primary Objective:

- To obtain clinical safety assessments of Illuminare-1, after intravenous administration, at specified time points (24 h post-injection, postoperative day  $10 \pm 5$  days, postoperative day  $30 \pm 5$  days and postoperative day  $45 \pm 10$  days).

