**Adverse Event Stopping Rules**

If >20% of patients within a cohort experience a grade 2 or higher adverse event that is considered attributable to the drug and clinically significant, dose escalation will be stopped at that level, and the prior dose level will be considered the maximum tolerated dose.

The exact rules are >1 out of 5 for the first five patients, >2 out of 10 in total when an additional five patients added and no more than 20% at any point after that.

Adverse events at the first postoperative visit for catheter removal ( $10 \pm 5$  days) will be used to determine whether dose escalation can proceed during Part 1 of the study

In Part 1, 5 patients will initially be observed at each dose level. If >20% of patients within a cohort experience a grade 2 or higher adverse event that is considered attributable to the drug and clinically significant, dose escalation will be stopped at that level, and the prior dose level will be considered the maximum tolerated dose. The exact rules are >1 out of 5 for the first five patients, >2 out of 10 in total when an additional five patients added and no more than 20% at any point after that. Adverse events at the first postoperative visit ( $10 \pm 5$  days) will be used to determine whether dose escalation can proceed during Part 1 of the study (see figure above). Based upon short half-life of the agent (approximately 4 hours) and our pre-clinical data, we do not expect to see dose limiting toxicities beyond 2 days after administration of the agent. The first patient receiving the drug will be observed for 30 days before proceeding with administration in other enrolled patients to observe for initial toxicities. We will continue to monitor for both expected and unanticipated toxicities with a phone follow-up at  $30 \pm 5$  day and in-person at the next scheduled clinic visit at  $45 \pm 10$  days. If more than 20% of patients in the first (lowest) cohort have a grade 2 or higher adverse event attributable to the drug, the trial will be stopped.

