##### 15.1.1.1 Renal Toxicity Stopping Criteria

Clinical chemistry threshold stopping criteria have been designed to assure subject safety. When subjects meet the following clinical chemistry criteria, additional testing will be performed, and the subject monitored until chemistries resolve, stabilize, or return to baseline values. The subject will not be withdrawn from the study since no further administration of the agent will be performed (it is a one-time use agent and will have already been given) and the data regarding fluorescent intensity of the nerve of interest will already have been obtained.

Patients with significant renal dysfunction (<60 mL/min as assessed by the Cockcroft Gault calculation for creatinine clearance) will not be enrolled on the trial as per initial exclusion criteria. Creatinine values will be obtained at 4 hours and 14 hours after surgery or as per standard of care after surgery. If creatinine assessments after administration of the investigational agent identify a doubling in baseline creatinine or a GFR < 50 ml/min/1.73m^2, the patient will be assessed to determine whether other likely etiologies for the renal dysfunction are present, such as acute blood loss, hypotension, administration of known nephrotoxic medications, etc. The primary investigator will coordinate these assessments with the primary team to determine whether the change in renal function is clinically significant and attributable to the investigational agent. Repeat renal function assessments will be made twice weekly until creatinine levels resolve, stabilize or return to within baseline values and the patient will be referred to a nephrologist for consultation.

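### The concomitant medication check stops within 24 hours of surgery, so no scheduled contact verifies the post-dose drug restrictions or records medication for attributing later adverse events

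*Protocol*

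**What the plan says.** The table in Protocol Section 11.0 has a separate row for "Concomitant medication check". It carries a mark at the preoperative visit and in the postsurgery column for the first 24 hours. The perioperative, 48 and 72 hour, day 10, day 30 and day 45 cells are empty.

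Several other sections look past that point:

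- Section 6.2 lists among the exclusions "Exposure to investigational agents in the immediate 30 days before or 15 days after study drug administration".
- Section 6.2 also allows a patient to stop an interfering phototoxic drug before dosing and requires the patient to stay off it "as well as for 48 hours after administration of Illuminare-1". The nonclinical part of Section 3.0 agrees that "precautions will be taken for the first 48 hours after drug administration". Section 10.0, item 11, instead has these drugs avoided "for 24 hours before and after administration of Illuminare-1".
- Section 15.0 defines causality partly by other treatment. The highest category requires that concomitant drugs do not explain the event, and the two below it refer to other therapy the patient received.
- Section 15.1.1.1 has a creatinine trigger followed by a search for other causes, "such as acute blood loss, hypotension, administration of known nephrotoxic medications, etc".
- Under the stopping rules in Section 4.2, adverse events at the day 10 visit "will be used to determine whether dose escalation can proceed during Part 1 of the study".
- The primary objective of Part 2 in Section 2.0 is "To obtain clinical safety assessments of Illuminare-1, after intravenous administration, at specified time points", and those time points run to day 45. Part 1 uses the same time points.

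**The concern.** A restriction that no contact is told to check cannot be shown to have been kept. The 15-day condition on investigational agents is written as an exclusion criterion, but its post-dose half cannot be known at enrolment, and nothing in the schedule returns to it. Patients go home the day after surgery, so a restarted or newly started drug would usually arise after the last scheduled check.

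The second issue is attribution. The trial has one arm, and a toxicity counts toward the stopping rules only if it is judged attributable to the agent. That judgement is meant to take account of other drugs. At the day 10 contact, which decides escalation, and at the day 30 and day 45 contacts, which complete the primary safety result, the schedule asks for no medication record. A toxicity could then be excused or counted on the basis of recall after the fact.

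**Working it through.** No sample size, power or error rate is involved. The check sets the schedule beside the restrictions and the attribution rules.

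**Step 1. The schedule (Section 11.0).**

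| Contact | Adverse events | Metabolic panel | Neurologic assessment | History and physical | Medication check |
|---|---|---|---|---|---|
| Preoperative | blank | X | X | X | X |
| Under 24 h | X | X | X | X | X |
| Day 10 ± 5 | X | X | X | X | blank |
| Day 30 ± 5, telephone | X | blank | blank | blank | blank |
| Day 45 ± 10 | X | X | X | X | blank |

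Adverse events are assessed at four contacts. The medication check is marked at one of them and missing from three.

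**Step 2. Restriction windows against the last check (taken as day 1).**

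- Investigational agents, Section 6.2: 15 − 1 = about 14 days without a scheduled check.
- Phototoxic drugs, Section 6.2: 48 − 24 = about 24 hours without a scheduled check.
- Phototoxic drugs, Section 10.0: 24 − 24 = essentially no gap.

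The phototoxic result depends on which section governs, and the sections disagree. The pre-dose side differs as well: five half-lives of the interfering drug in Section 6.2, 24 hours in Section 10.0. The investigational-agent result does not depend on this conflict.

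**Step 3. Where later medication information could come from.**

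- *The history and physical at day 10 and day 45.* Section 9.0 includes medications in the history, but only for the pretreatment examination. In the table, the history and the medication check are separate rows. Both are marked preoperatively and under 24 hours; only the history is marked at days 10 and 45.
- *The call within 2 days of surgery.* Section 10.0, item 12, describes it as a toxicity evaluation. No medication review is mentioned.
- *The day 30 call.* Neither row is marked. Section 4.2 also holds the first patient for 30 days before others are dosed.
- *For-cause work-up.* Section 15.1.1.1 orders an inquiry after a creatinine trigger. Sections 4.2, 9.0 and 15.0 order a neurologic assessment of relatedness after a change in score. These begin once an event is seen.

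**Step 4. Sensitivity of the decision rule (Sections 4.2 and 14.0).** A dose level stops at more than 1 of 5, then at more than 2 of 10. Reattributing one event gives:

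- 2/5 = 40% (stop) becomes 1/5 = 20% (no stop for toxicity).
- 3/10 = 30% (stop) becomes 2/10 = 20% (no stop for toxicity).

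This shows how much one attribution can matter. It does not estimate how often one would be wrong.

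**The case against.** The strongest reply is that the protocol does not leave attribution blind. A clinician sees the patient at days 10 and 45 and takes a history. A creatinine trigger brings a search for nephrotoxic drugs, twice-weekly renal function tests and a nephrology referral. A change on the neurologic instruments brings a full assessment of relatedness, and grade 2 or higher neurotoxicity brings a specialist examination. The causality definitions themselves direct attention to other therapy. All of this stands. A reader might infer from the empty cells that the investigator must attribute events without medication data; the documents do not support that. What is missing is a scheduled, prospective record, not any means of asking.

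The phototoxic argument is also weaker than it looks. Patients stay in hospital for about 24 hours after dosing, and a footnote to the table lets the adverse event evaluation in the under-24-hour column take place by telephone within 2 days of surgery. That footnote belongs to the adverse event row and does not extend to medications, but it shows that the column is not strictly literal. Under Section 10.0 the gap all but disappears.

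For neurologic events, the dependence on medication follows from the general causality definitions and from the entry exclusion of neurotoxic drugs. Section 15.1.1.2 does not mention medication.

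**Conclusion.** The point holds as a gap in data collection. As written, no scheduled contact verifies the post-dose restrictions, and no medication check is scheduled at three of the four contacts where adverse events are assessed. For days 10 and 45 this is partly offset by a history of unstated content and by for-cause inquiry; for the day 30 call there is no scheduled history either. About 14 of the 15 days for investigational agents are unverified. For phototoxic drugs the gap is about 24 hours under Section 6.2 and essentially nil under Section 10.0. These figures assume that the under-24-hour check takes place by day 1.

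Two stronger readings should be resisted. A reader might note that the safety period can reach day 55 (45 + 10), that another agent could be started 20 to 40 days before the day 30 and day 45 windows close (35 − 15 and 55 − 15), and conclude that this distorts escalation. It does not: escalation, and the continuation assessment for Part 2 described in Section 4.2, use events through the day 10 visit, at latest day 15 (10 + 5), which the 15-day bar covers. A reader might also infer that the bar is too short. Its length is a design choice that contradicts nothing in the protocol. The protocol expects clearance before day 7 and no dose-limiting toxicity beyond day 2.

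This is a worthwhile, inexpensive improvement. It does not invalidate the design.

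**What to change.** - In the Section 11.0 table, mark the concomitant medication check at the telephone call within 2 days of surgery and at the day 10, day 30 and day 45 contacts. Record start and stop dates, so that each contact covers the interval since the previous one, including any part of the phototoxic window that falls after the early call.
- State in Section 15.0 that this record is reviewed whenever a grade 2 or higher event is attributed.
- Move the post-dose half of the 15-day investigational-agent condition out of the exclusion criteria, and state it as a post-dose restriction verified at follow-up.
- Reconcile the phototoxic-drug windows in Sections 6.2 and 10.0, and the precaution period in Section 3.0. This review takes no position on which window is right.

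The cost is a few minutes and slightly more data entry per contact. No new visit or procedure is needed.
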